### Data collecting and monitoring

2.14

All baseline assessment, end of 2-month intervention, 3 months post-intervention data will be collected by the CRC blind to the treatment modality or treatment groups. All subjects’ adverse events and additional treatment during the follow-up period will also be recorded.

This trial uses a paper-based case report form (CRF) and an electronic data management system. All data will be recorded by CRC in CRFs. Completed CRFs are reviewed by Clinical Research Associate (CRA), from a third-party company, independent of the research team and blinded to group allocation. All data administrators have data analysis qualifications and are trained uniformly. To ensure the accuracy of the data, 2 data administrators independently enter the information and proofread it. If there are issues with the information in the CRF, the CRA can fill out a query sheet and give it to the CRC and site PI. The CRC can then modify the data according to any revisions made by the site PI. After confirming that the database is correct, the site PI, CRC, and statistician will lock the database.

All documents that contain participants’ personal information will be identified by code number and stored separately. Only researchers involved in this study can be available to the confidential documents.

All study data, including the paper-based documents and electronic data, will be stored at each site for 5 years after the completion of the trial.

Because the study is not a drug trial and the sponsor or funder has no access to the raw data, a data monitoring committee will not be formed, and there is no planned trial audit. Besides, there are no interim analyses and stopping guidelines due to the very low risks of adverse events and other unintended effects.

### Quality control

2.15

Quality control will be carried out throughout the trial to maintain quality. Monitoring information will be regularly submitted to the site PI and retained for future reference. The steering committee, composed of the 3 research centers’ PI, a statistician, and a foundation lead, is responsible for the coordination, development, and quality control of all the programs in the trial. All researchers must receive professional training on the trial method, study technique, and the method used for regular monitoring before participating in the trial. The therapist will be tested after training to ensure consistency of methods. The steering committee will discuss any modifications or corrections to the study protocol and submit them to the ethics committee for approval. Detailed records of changes will be kept.

### Statistical analyses

2.16

The analysis set will consist of a full analysis set (FAS), a per-protocol set, and a safety set. The safety set will include randomly assigned participants and receive at least one intervention treatment. The FAS will consist of data indicating that the treatment was as close to the intention to treat as possible. In addition to meeting the safety set criteria, the participants must have been evaluated for the primary outcome at least once at the baseline. The FAS will be used in the primary analysis. For missing data, we will analyze the underlying reason and use an imputation adjustment approach, and the last observation carried forward analysis will be used to handle the missing data. After the primary analysis, a sensitivity analysis will be performed by comparing the results from the per-protocol analysis and the intention to treat analysis to evaluate the impact of missing data on the trial results. Besides, subgroup analyses by the center will be done.

(1)Statistical analysis methodFor all of the analyses, SAS version 9.4 was used. The confidence interval will be established at 95%, and the significance level at 0.05.Continuous variables were analyzed with an ANOVA test if normally distributed (results are presented as means ± SD) or Kruskal-Wallis H test if not normally distributed (presented as median with interquartile range). Multiple comparisons were addressed using the Tukey post hoc test (for ANOVA), and Bonferroni correction (for Kruskal–Wallis). The classification count data is checked by the chi-square test. This study used a one-sided test. When *P* < .05, the difference was considered statistically significant.(2)Statistical analysis contenta.Baseline evaluation: Social demographic characteristics, baseline severity analysis.b.Efficacy evaluation: We use the low back pain VAS score sheet, spinal ROM sheet, ODI scale, SF-36 scale, and the number of treatment sessions.c.Safety evaluation: Evaluation was made by the incidence of adverse events or recurrence of pain, or further injury from accidents during the follow-up period, and the level of safety.d.Compliance evaluation: Evaluation was carried out using the compliance rate.

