### Suspension criteria

2.6

Subjects may discontinue from the study after discussions with the clinicians for the following reasons:

(1)The subject has an adverse reaction to the intervention.(2)The subject's pain score decreased to 0.(3)The subject wishes to withdraw from the clinical study.(4)The subject wishes to attend other interventions, which may result in the study bias, such as attending chiropractic or other massage therapy or non-traditional spinal treatment.

Those who meet any of the above suspension criteria shall be suspended. However, all subjects’ responses will be recorded to determine the reasons for suspension from the study and the intention-to-treat analysis.

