### Blinding

2.9

Due to the inability to blind patients, the practitioners, physiotherapists, and patients are not blinded.

The assessment of clinical efficacy will be performed by a clinical assessor who will be masked to the treatment assignment. The clinical researcher, assessor, and statistician do not share study information during this clinical trial.

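### The primary analysis set leaves out randomised patients who never start treatment, which in an unblinded trial cannot be assumed neutral between arms

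*Protocol article*

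**What the plan says.** All of the set definitions are in section 2.16 (Statistical analyses) of the protocol article.

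- Three sets are named: "The analysis set will consist of a full analysis set (FAS), a per-protocol set, and a safety set".
- The safety set carries a treatment condition: "The safety set will include randomly assigned participants and receive at least one intervention treatment".
- The FAS inherits that condition and adds a baseline measurement: "In addition to meeting the safety set criteria, the participants must have been evaluated for the primary outcome at least once at the baseline". No post-baseline VAS is required.
- The FAS has a stated aim, "The FAS will consist of data indicating that the treatment was as close to the intention to treat as possible", and a stated use, "The FAS will be used in the primary analysis".
- Missing values are to be handled by last observation carried forward (LOCF). A sensitivity analysis compares per-protocol with intention-to-treat results.

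Two other sections bear on the point. Section 2.9 (Blinding) states that "the practitioners, physiotherapists, and patients are not blinded". Section 2.6 (Suspension criteria) says that the responses of all subjects will be recorded, both to establish why participation was suspended "and the intention-to-treat analysis".

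**The concern.** Receiving a first session happens after randomisation. Patients in this trial are not blinded, and the three arms (Tuina, physiotherapy, or both) are plainly different to the person receiving them. A patient who hoped for one treatment and drew another may not attend. If that happens more often in one arm, or if different kinds of patient fail to start in different arms, then those who remain in the FAS are no longer the groups that randomisation created.

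Dropping patients who were never treated is easiest to defend when neither patient nor therapist knows the allocation, because starting cannot then depend on it. That defence is not available here. The condition is also unnecessary for the aim the protocol sets itself: randomisation and a baseline VAS would be enough to define a set closer to intention to treat. What is at stake is the randomised basis of the primary comparison, for however many patients never start.

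**Working it through.** **1. Who is in and who is out.** Applying the section 2.16 rules to each kind of randomised patient with a baseline VAS:

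| Patient | Safety set | FAS (primary) |
|---|---|---|
| Completes all 6 sessions | in | in |
| Attends one session, then stops | in | in |
| Treated at least once, no later VAS | in | in (LOCF applies) |
| Randomised, no sessions | out | **out** |

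Only the last row is affected. Recording the responses of suspended subjects (section 2.6) does not alter it, because FAS membership is still decided by the treatment condition.

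**2. The plan's own figures.** Section 2.7 gives mean (SD) VAS changes of 1.4 (0.8) for Tuina, 1.9 (0.9) for the combination and 1.65 (0.85) for physiotherapy. With a common SD of 0.85, a one-way ANOVA at α = 0.05 and 57 per group has noncentrality

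57 × [(−0.25)² + 0.25² + 0²] / 0.85² = 57 × 0.125 / 0.7225 = 9.86,

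and power 80.2%. So the stated 57 is reproduced. Then 57 / (1 − 0.15) = 67.06, rounded up to 68 per group; 68 × 3 = 204 per centre; 204 × 3 = 612. Over the three centres each arm also has 68 × 3 = 204. The sample size is not in dispute here.

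**3. How far the exclusion could move a contrast.** Let r be the share of an arm that never starts, and g the difference in mean change between that arm's never-starters and its starters. Leaving never-starters out shifts the arm mean by r × g. Between two arms the shift is r₁g₁ − r₂g₂. It is zero when r and g are the same in both arms. With a common g it is (r₁ − r₂) × g.

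The document gives neither r nor g, so both are assumptions. I take g as 0.5 SD (0.425) or 1 SD (0.85) and vary the between-arm difference in non-start. The reference values are the planned Tuina–physiotherapy difference, 1.65 − 1.4 = 0.25, and the standard error of a pooled two-arm contrast, 0.85 × √(2/204) = 0.084.

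| Assumed difference in non-start | Patients of 204 | Shift, g = 0.425 to 0.85 | Share of 0.25 | In standard errors |
|---|---|---|---|---|
| 0 points | 0 | 0 | 0% | 0 |
| 2 points | about 4 | 0.009 to 0.017 | 3% to 7% | 0.1 to 0.2 |
| 5 points | about 10 | 0.021 to 0.043 | 9% to 17% | 0.25 to 0.5 |
| 10 points | about 20 | 0.043 to 0.085 | 17% to 34% | 0.5 to 1.0 |

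The sign depends on which arm loses more patients and whether they would have done better or worse, which nothing in the document settles.

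**4. What happens if never-starters are put back and nothing else changes.** A never-starter with no later VAS would have the baseline carried forward, that is, a change of zero. With 5% such patients in physiotherapy and none in Tuina, the physiotherapy mean falls by 0.05 × 1.65 = 0.083, which is 33% of 0.25. The same 5% in Tuina alone lowers that mean by 0.05 × 1.4 = 0.07, or 28% of 0.25. These figures show how sensitive the result is to the imputation rule; they do not measure the bias from exclusion. They do show that redefining the set without attending to the missing outcomes could move the contrast more than the 5-point row above.

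**The case against.** The strongest case on the other side has four parts.

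*The rule is fairly inclusive.* One session and a baseline VAS are enough, with no post-baseline value needed. That is wider than a set requiring a follow-up measurement. This stands, and it limits the defect to patients with zero sessions.

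*The effect may be negligible.* All three arms receive active treatment, no refusal rate is given, and a 5-point imbalance yields at most about half a standard error of the pooled contrast. This stands as to size. It does not make the rule neutral, because no one can say in advance that non-start will be balanced.

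*The intention-to-treat population may be defined elsewhere.* A reader might infer that the planned intention-to-treat analysis is itself the treated-only FAS, since no other set could serve. The document does not support stating that as fact. It says the FAS is to come close to intention to treat, which suggests the two differ, and it never gives the FAS that label. The article is condensed, and a separate definition may sit in the full protocol or analysis plan. What remains is the explicit condition on the FAS, which is the primary set whatever the other analysis turns out to be.

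*Nothing shows that patient preference drives attendance.* A reader might also take this to be a preference trial. It is not described as one; it is an ordinary randomised trial without blinding of patients. That patients know their arm before the first session is itself an inference from the unblinded design, though a natural one.

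**Conclusion.** The point holds on the text. A stated rule, not an omitted detail, removes randomised patients from the primary analysis because of an event that allocation can influence, and this does not match the protocol's own description of the FAS. It concerns never-treated patients only.

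Neither the size nor the direction can be derived from the document. The 0.02 to 0.04 figure rests wholly on an assumed 5-point difference in non-start and an assumed gap of 0.5 to 1 SD, and should not be read as an estimate of bias in this trial. With few or balanced non-starters the effect would be trivial.

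Severity: should-fix. I am confident in the reading of the rule, much less so in its practical consequence.

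**What to change.** 1. Define the primary analysis set as all randomised participants with a baseline VAS, analysed in the arm allocated, regardless of sessions received.
2. Keep the condition of at least one treatment for the safety set only.
3. State that the set in item 1 is the one meant by the intention-to-treat analysis in sections 2.6 and 2.16.
4. Seek the 8-week VAS from never-starters at the scheduled end-of-intervention assessment.
5. For never-starters without that value, do not rely on LOCF alone; add a sensitivity analysis under another missing-data assumption.

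The cost is a short amendment to section 2.16, a little more follow-up and analysis work, and slight dilution of the treatment contrast by untreated patients. Amending the set definition alone would be incomplete, for the reason shown in step 4 of the working. The planned total of 612 does not change. The amendment should be settled before database lock, so that the choice of population cannot be influenced by knowing who failed to start.

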**Figure 1 F1:**
[figure not shown]
Flow chart of the study. A total of 612 participants will be randomized to the 3 groups. The study period will consist of the baseline, end of 2-month intervention, 3 months post-intervention. FAHJNU = First Affiliated Hospital of Jinan University, MC = Mayo Clinic, SGH = Singapore General Hospital.

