### Sample size calculation

2.7

This is a randomized controlled trial with 3 parallel arms. The test groups are the TN and T&P groups; the control group is the PT group. The visual analogue scale (VAS) score is the primary outcome. We use ANOVA to calculate the sample size. According to the previous report,^[24]^ the mean (standard deviation) difference of the VAS score of pre- and post-treatment in the TN group, T&P group, and PT group is 1.4 (0.8), 1.9 (0.9), and 1.65 (0.85), respectively. Assuming *α* = 0.05 (2-sided), *β* = 0.80, 171 subjects (57 subjects per group) are needed to achieve an 80% probability of detecting difference (PASS software, Ver. 11, NCSS, LLC. Kaysville, Utah; www.ncss.com). When considering a potential dropout risk of 15%, a total of 204 subjects (68 subjects per group) will be required as a sample size for statistically significant results at each center.

Stratified by 3 centers, the combined sample size is 612 for a meta-analysis.

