### Outcome measurements

2.11

The primary outcome measure assesses the efficacy of massage therapy for the treatment of CNLBP: change in low back pain measured by the 100 mm VAS^[31]^ over the 2-month treatment. Secondary outcome measures included the Oswestry Disability Index^[32]^ (ODI), spinal range of motion^[33]^ (ROM), and the 36-item short-form health survey^[34]^ (SF-36). Fig. 2 demonstrates all measurements and measuring time points.

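### LOCF is the only missing-data method named and, on the visits listed, would score a treated patient without a 2-month VAS as unchanged; comparing per-protocol with ITT is not an adequate check

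*Protocol article*

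**What the plan says.** Section 2.16 makes the FAS the primary analysis set. Entry needs at least one treatment, and "the participants must have been evaluated for the primary outcome at least once at the baseline"; no later value is required.

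For missing data the same section says "we will analyze the underlying reason and use an imputation adjustment approach", and then that "the last observation carried forward analysis will be used to handle the missing data". The first phrase names no method, so LOCF is the only concrete one.

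The stated check is a sensitivity analysis "comparing the results from the per-protocol analysis and the intention to treat analysis to evaluate the impact of missing data".

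The primary outcome (section 2.11) is change in VAS pain "over the 2-month treatment". On timing, the Figure 1 caption says "The study period will consist of the baseline, end of 2-month intervention, 3 months post-intervention", and section 2.14 gives the same three time points: "All baseline assessment, end of 2-month intervention, 3 months post-intervention data will be collected by the CRC". Section 2.11 refers to Figure 2 for all measuring times; that figure is not shown in the text at hand.

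Section 2.6 lists a pain score that has fallen to 0 among the reasons for stopping. It says that suspended subjects' responses are recorded for the ITT analysis, but not that the 2-month VAS is still taken.

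**The concern.** LOCF needs an earlier value to carry. With one baseline and one end-of-treatment assessment, the only earlier value for the primary endpoint is the baseline itself, so the imputed change is exactly 0. The sample-size section expects substantial mean improvement in every arm, so 0 is not a neutral guess. LOCF also treats the filled value as if it had been observed.

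A patient who stops because pain has gone, with no VAS afterwards, would be recorded as not having improved at all. Patients and therapists are not blinded, and leaving for other treatment is a listed reason for stopping, so dropout that depends on arm or outcome is plausible.

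Two things are at stake. With equal dropout, the treatment contrast shrinks and power is lost. With unequal dropout, the contrast is biased in a direction nobody can predict, and a false difference can arise where there is none. The planned check does not vary the missing-data assumption within one population.

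**Working it through.** **Inputs from section 2.7.** Mean change (SD): TN 1.4 (0.8), T&P 1.9 (0.9), PT 1.65 (0.85). Two-sided α 0.05, power 80%, 57 per arm, 15% dropout, 68 per arm at each centre. Three centres give 204 per arm.

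**Reproducing the plan.** One-way ANOVA, noncentral F, common SD 0.85:
- Sum of squared deviations of the means = 0.25² + 0.25² + 0² = 0.125.
- Noncentrality at n = 57: 57 × 0.125 / 0.85² = 9.86, giving power 0.802. The stated 57 reproduces.
- 57 / 0.85 = 67.06, rounded up to 68. This inflation treats dropouts as not evaluable. With 68 × 0.85 ≈ 58 evaluable per arm, power is 0.81.

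**Baseline carried forward.** If a fraction d of an arm is set to change 0:
- mean = (1 − d)μ
- variance = (1 − d)σ² + d(1 − d)μ²

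**Equal dropout, d = 0.15:**
- Means: TN 0.85 × 1.4 = 1.19; T&P 0.85 × 1.9 = 1.615; PT 0.85 × 1.65 = 1.4025.
- Variances: TN 0.85 × 0.64 + 0.1275 × 1.96 = 0.794; T&P 0.85 × 0.81 + 0.1275 × 3.61 = 1.149; PT 0.85 × 0.7225 + 0.1275 × 2.7225 = 0.961. The mean variance is 0.968, so the SD is 0.984.
- The T&P minus TN contrast falls from 0.50 to 1.615 − 1.19 = 0.425.

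| Zeros per arm | Power, 68 per arm | Power, 204 per arm |
|---|---|---|
| 5% | 0.78 | >0.99 |
| 10% | 0.69 | 0.99 |
| 15% | 0.60 | 0.98 |
| 20% | 0.52 | 0.96 |

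At 15% zeros, 105 per arm would be needed for 80% power.

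**Unequal dropout, no true difference.** Assume mean 1.65 and SD 0.85 in every arm, with dropout of 10%, 15% and 20%. The protocol gives no rates by arm.
- Means: 0.90 × 1.65 = 1.485; 0.85 × 1.65 = 1.4025; 0.80 × 1.65 = 1.32.
- False maximum difference: 1.485 − 1.32 = 0.165, one third of the 0.50 contrast that drives the ANOVA.
- Omnibus rejection: 13% at 68 per arm and 31% at 204 per arm, against a nominal 5%. It rises with sample size, so pooling the centres makes it worse.

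**Unequal dropout, design effects.** These rates are also assumed.
- TN 10%, T&P 20%, PT 15%: contrast 1.52 − 1.26 = 0.26; power 0.26 per centre and 0.66 pooled.
- TN 20%, T&P 10%, PT 15%: contrast 1.71 − 1.12 = 0.59, larger than the true 0.50.

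**The planned check.** The per-protocol and ITT sets differ in adherence and in who is included, as well as in missingness. A difference between their results could come from any of these. Agreement could occur while dropout depends on outcome in both sets.

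**The case against.** **Figure 2 is not visible.** It may schedule a VAS during treatment. Stopping at a pain score of 0 implies that some pain score is taken after baseline, and section 2.12 has symptoms reviewed before and after each session. If dropouts carried forward half their arm's response (half the mean and half the SD, assumed), per-centre power at 68 per arm would be 0.81, not 0.60. This stands: change 0 follows from the listed visits but is conditional on the figure. LOCF would still be a single imputation treated as observed.

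**The trial as a whole is not left with 60% power.** A reader might infer that from the 0.60. The combined sample is 612, centre also appears as a subgroup analysis, and pooled power with 15% zeros is 0.98. The 0.60 matters because section 2.7 sizes each centre to reach significance on its own.

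**15% zeros is an upper bound at the planned dropout rate.** Patients who leave before any treatment are outside the FAS, and some who stop may still give a 2-month VAS. This stands.

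**The check is not worthless.** It is tempting to say that comparing per-protocol with ITT can reveal nothing. If the per-protocol set excluded patients without a 2-month VAS (its definition is not given), it would be close to a complete-case analysis, and under equal dropout unrelated to outcome could show about 0.50 beside 0.425. The two results could therefore diverge visibly, but the cause could not be identified.

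**LOCF is not the whole stated plan.** The undefined imputation approach may be detailed in an analysis plan that is not shown. That does not remove the commitment to LOCF, and the two statements need reconciling.

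**Conclusion.** The concern holds in conditional form. Section 2.16 commits the primary analysis to LOCF in a set that admits patients with only a baseline VAS. On the visits listed, and unless Figure 2 adds a VAS during treatment, such patients count as unchanged.

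With equal dropout the harm is shrinkage and lost power, not false positives: up to 0.075 off the 0.50 contrast, and per-centre power of 0.60 instead of 0.81, with pooled power barely touched. With unequal dropout the bias can go either way and the false-positive rate can exceed its nominal level, but the size of this rests on assumed rates, since the protocol gives only 15% overall. The per-protocol comparison does not serve the purpose stated for it: a difference cannot be attributed to missing data, and agreement does not exclude outcome-dependent dropout.

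The calculations take the design means and SDs as being in one common unit; power does not depend on which. They use the two-sided α of the sample-size section.

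**What to change.** In section 2.16:

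1. Replace LOCF with multiple imputation by arm, using baseline VAS, centre and any post-baseline pain scores collected. A likelihood-based repeated-measures model is an alternative only if VAS is measured at a further post-baseline visit. Section 2.13 describes the week-20 contact as a telephone call about recurrence, so a week-20 VAS should not be taken for granted.
2. Reconcile this with the undefined imputation approach, so that one primary method is named.
3. Make delta-adjusted (tipping-point) imputation, in the FAS or in all randomised patients, the missing-data sensitivity analysis.
4. Keep the per-protocol analysis as supportive only, not as the test of missing-data impact.

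It would also help to state in the text whether a VAS is taken during treatment and whether the 2-month VAS is sought from patients who have stopped.

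The analysis changes need no new data. They cost rewording, some extra programming and slightly wider intervals than single imputation gives. They should be made before database lock.

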## Introduction

1

Low back pain (LBP) is a common clinical symptom prompting patients to seek medical care. 80% of adults experience LBP during their lifetime.^[1]^ It is the leading cause of disability worldwide, with a global prevalence of 7.3% in 2016.^[2]^ Usually, most people recover with or without treatment, however, a relapse of the pain is common and 10% to 15% of LBP patients may develop chronic low back pain (CLBP).^[3]^ CLBP can be categorized into sciatica/nerve root pain syndrome, specific low back pain, and non-specific low back pain.^[^4^,^^5^^]^ The common causes of CLBP can include spinal injury, lumbar muscle strain, degenerative spinal intervertebral disc and vertebra joints, and kidney disease in women. 90% of CLBP patients do not have a clearly identifiable cause of pain, classified as chronic non-specific low back pain (CNLBP).^[^6^,^^7^^]^ CNLBP refers to pain and discomfort localized in the area between the costal margin and the inferior gluteal fold, not resulting from an identifiable or known specific pathology, with or without referred leg pain of >12 weeks’ duration.^[^8^,^^9^^]^ CNLBP's symptom onset, recovery, and clinical outcomes are influenced by biological, psychological, and social factors; therefore, its management is often complicated and multimodal.^[10]^

As the pathoanatomical cause of CNLBP remains an enigma, no specific evidence-based clinical practice method has been recommended for medical providers to manage CNLBP.^[^11^,^^12^^]^ According to the Consensus on the management of LBP,^[13]^ there is a wide variety of approaches recommended for CNLPB, such as patient education, self-management, physiotherapy, psychological therapy, medication, injection, ablation techniques, or surgery. Although these treatments have shown some efficacy, there is no conclusive evidence for their continued use in the mainstream medicine or sufficient knowledge of the extent of their side effects.^[12]^ Nonetheless, a multidisciplinary eclectic rehabilitation strategy is often recommended for patients with CNLBP.^[14]^ More and more people have turned their attention to complementary and alternative medicine (CAM) treatment.^[^15^,^^16^^]^ At present, Tuina therapy has been widely accepted as a CAM modality.^[17]^

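### LOCF is the only named missing-data method for the primary analysis: it shrinks true contrasts and, if dropout differs by arm, can create a false one

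*Protocol article*

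**What the plan says.** Section 2.16 (Statistical analyses) deals with missing data in one sentence. It first says "we will analyze the underlying reason and use an imputation adjustment approach", without a model, variables or assumption, and then says "the last observation carried forward analysis will be used to handle the missing data". LOCF is the only method named, and its relation to the other approach is not explained.

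The same section says "The FAS will be used in the primary analysis". To enter the FAS a patient must have been randomised and treated at least once, and beyond that "the participants must have been evaluated for the primary outcome at least once at the baseline". No post-baseline value is required. The one check on missing data is described as "comparing the results from the per-protocol analysis and the intention to treat analysis to evaluate the impact of missing data on the trial results".

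The primary outcome (2.11) is the change in VAS over the 2-month treatment. The Figure 1 legend says "The study period will consist of the baseline, end of 2-month intervention, 3 months post-intervention". Section 2.11 refers to Figure 2 for all measuring times; that figure is not shown in the text at hand.

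Three further statements matter:

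- Section 2.7 plans for 15% dropout, with no split by arm.
- Section 2.9 says "the practitioners, physiotherapists, and patients are not blinded".
- Section 2.6 lists reasons for stopping that are tied to outcome: an adverse reaction, a pain score of 0, or a wish for other treatment.

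**The concern.** LOCF replaces a missing score with the last recorded one. If the visits are only those in the Figure 1 legend, the last score of a patient lost before the end of treatment is the baseline score, so that patient's primary outcome is a change of exactly zero. The arm mean then mixes the pain relief of those who stayed with a block of zeros whose size is the dropout rate.

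Two consequences follow. If all arms lose the same share, every arm mean shrinks by that share, and so does every true contrast. If the arms lose different shares, the means differ even when the treatments are equally good. Unequal loss is plausible here because patients and therapists know the treatment and because several stopping reasons depend on how the patient is doing. More patients do not remove such a difference; they make it more likely to reach significance.

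**Working it through.** **Inputs.** From 2.7: mean (SD) VAS fall TN 1.4 (0.8), T&P 1.9 (0.9), PT 1.65 (0.85); alpha 0.05; dropout 15%; 68 per arm per centre, hence 68 × 3 = 204 per arm over three centres. Section 2.7 gives no unit for these falls, but the rejection rates depend only on the ratio of mean to SD. Assumptions, not in the documents: dropout by arm, the share of the gain that is carried, and dropout unrelated to outcome.

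**The plan's own figure.** One-way ANOVA, three means 1.4, 1.9, 1.65 (grand mean 1.65), common SD 0.85, n = 57 per arm: noncentrality = 57 × (0.25² + 0.25² + 0) / 0.85² = 57 × 0.125 / 0.7225 = 9.86, power 0.802. Then 57/0.85 = 67.06, rounded up to 68; 68 × 3 × 3 = 612. The stated sample size is reproduced and is not in dispute.

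**Arm mean under LOCF at 8 weeks, baseline carried.** With dropout d, true mean μ and SD σ:

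- mean = (1 − d)μ
- variance = (1 − d)σ² + d(1 − d)μ²

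**Equal 15% dropout.** T&P minus TN becomes 0.85 × 0.50 = 0.425. T&P minus PT becomes 0.85 × 0.25 = 0.2125. The variance also rises:

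- T&P: 0.85 × 0.81 + 0.1275 × 3.61 = 1.149
- PT: 0.85 × 0.7225 + 0.1275 × 2.7225 = 0.961

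At 204 per arm the standard error of T&P minus PT is √(2.110/204) = 0.1017, so unadjusted pairwise power is Φ(0.2125/0.1017 − 1.96) = 0.55. With observed values only (204 × 0.85 = 173.4 per arm) the standard error is √(1.5325/173.4) = 0.0940 and power is Φ(0.25/0.0940 − 1.96) = 0.76.

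**Unequal dropout, no true effect.** With a mean fall of 1.65 in every arm, the false gap between the extreme arms is 1.65 × (d₂ − d₁): 1.65 × 0.06 = 0.099 for 12% against 18%, and 1.65 × 0.10 = 0.165 for 10% against 20%. The latter is two thirds of the 0.25 planning difference between PT and TN. Simulated rejection of the three-arm ANOVA at 5% (SD 0.85; ranges show simulation error):

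| Dropout by arm | Carried value | 68 per arm | 204 per arm |
|---|---|---|---|
| 15/15/15% | baseline | 5% | 5% |
| 12/15/18% | baseline | 7–8% | 13–14% |
| 10/15/20% | baseline | 13–14% | 31% |
| 12/15/18% | half the gain | 6% | 8% |
| 10/15/20% | half the gain | 7–8% | 13% |

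**Unequal dropout, planning means.** The direction depends on which arm loses more. If T&P loses 10% and PT 20%, the contrast reads 1.9 × 0.9 − 1.65 × 0.8 = 0.39. Reversed, it reads 1.9 × 0.8 − 1.65 × 0.9 = 0.035. The true value is 0.25.

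**Three months.** Let e be the share lost before week 8 (baseline carried), l the share lost after it (week-8 gain carried), and r the share of the gain truly kept. The error in an arm's mean fall is (1 − e − l)rμ + lμ − rμ = μ[l(1 − r) − er]. With μ = 1.65, r = 0.5 (assumed) and 15% lost in total, the error is +0.12 if all loss is late, 0 if it is split evenly, and −0.12 if all is early.

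**The case against.** The strongest reply is that nothing shows this trial will have unequal dropout. The protocol gives one rate, 15%, and at equal rates the false-positive rate stays at 5%. That stands: every inflated figure above rests on an assumed split, and a reader should not infer that the arm contrasts are biased as a matter of fact. More extreme splits give far larger rates, but the protocol offers no reason to expect them.

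Zero-change scoring is also not certain. A pain score of 0 as a stopping reason (2.6) and the symptom review at each session (2.12) suggest that pain may be scored during treatment. If so, LOCF carries part of the gain; the lower rows of the table show a smaller effect of the same kind. Section 2.6 also says that responses of suspended patients will be recorded for the intention-to-treat analysis, so stopping treatment need not mean a missing score. And if those who leave truly gained little, carrying baseline is near the truth.

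A reader might infer that LOCF hides relapse at 3 months and overstates durability. The documents do not support a direction: early losses understate relief and late losses overstate it. The Introduction's remark that "a relapse of the pain is common" describes low back pain in general, before some patients become chronic; it is not evidence of relapse after treatment in this population. Section 2.13 describes week 20 as a telephone enquiry about recurrence, and no tested week-20 VAS contrast is stated.

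A reader might also infer that the unnamed imputation approach will be picked after the reasons for loss are seen. The article does not say so, and an analysis plan may specify it.

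The per-protocol comparison has some value: if loss is unrelated to outcome, an analysis of observed patients could expose the artefact. But it changes who is analysed and does not directly vary the LOCF assumption.

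**Conclusion.** The point holds as a weakness in the stated primary method that should be fixed, not as a demonstrated bias. LOCF is the only method named, and it applies to an analysis set that admits patients with no post-baseline score.

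The shrinkage needs no unequal dropout: if baseline is carried and those lost would have gained as much as those who stayed, 15% loss removes 15% of each true contrast. The false difference does need unequal dropout. For the two assumed splits it raises the ANOVA false-positive rate to between about 13% and 31% at 204 per arm and between about 7% and 14% at 68, or to about 8–13% and 6–8% if half the gain is carried. The direction cannot be known in advance, either at 8 weeks or at 3 months.

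**What to change.** In 2.16, replace LOCF as the primary method with one of the following, and name it in place of the unspecified imputation approach:

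- a mixed model for repeated measures on VAS change, with arm, visit, arm-by-visit, baseline VAS and centre; or
- multiple imputation by arm, using baseline VAS, centre, adverse reactions and the reason for suspension.

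The mixed model gains little from patients who have only a baseline value, and both methods assume data missing at random. Because the stopping reasons in 2.6 are related to outcome, add a sensitivity analysis that departs from that assumption, for example delta-adjusted imputation. Keep LOCF at most as a labelled supplementary analysis.

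The cost is wording and a little more analysis work in SAS 9.4, which the plan already uses. No new patients or data are needed. The change should be made before the database is locked.
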